### Sample size

We estimated there would be 2,403 adolescents aged 13 to 18 years and registered at SES or SEU, based on Education Department data from the year prior to study commencement. Approximately 80% of these adolescents would have intellectual disability; meaning approximately 1900 students would be eligible for the study. We estimated that around 60% of schools would choose to participate in the study, and that within each school 95% of eligible individuals would participate. Consequently we expected to have a total sample size of around 1,000 adolescents (80% x 60% x 95% of 2403). We estimated participants would be grouped into around 50 clusters (assuming that an average of 20 (SD = 7.5) adolescents with intellectual disability would attend any one school). Thus we expected that each of the intervention and usual care groups would comprise 500 students from 25 schools.

One of the primary outcomes of interest is detection of vision or hearing impairment, which previous studies have shown has a current rate of around 10% in this population
[12,13]. With an assumed intra-class correlation coefficient (ICC) of 0.03, the design effect for this analysis is 1.57, without consideration of matching. On this basis, the study would have 90% power to detect an increase in the detection of vision impairment to 19% due to the intervention, at the 5% level of significance. For a condition with a current impairment rate of 20%, the study will have 90% power to detect an improvement to around 30% through the intervention. The matched-pairs design will have greater power, depending on the within-pair correlations, so the above estimates are conservative. The assumption of a maximum 0.03 for the ICC is plausible, based on a reported ICC (0.01) in an adult population
[7]. For analyses of major subgroups, e.g. examining increases within adolescents with Down syndrome, an estimated 25% of the sample distributed across clusters, the study would have 80% power to detect increases of 10% to 24%, or 20% to 37%.

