#### Quantitative

Percentages of detection of health screenings and health promotion activities initiated, and responses to postal questionnaires will be compared between the intervention and the usual care group using data extracted from medical records. The individual will be the unit of analysis. For continuous outcome variables, a mixed-effects linear regression model will be used to compare the outcomes between comparison groups, with allowance made for cluster and matching effects. For categorical outcomes, a mixed-effects logistic regression model will be used. Sub-group analysis of adolescents at particular risk, such as those with Down syndrome will also be performed.

The primary analyses will be based on the ‘intention-to-treat’ (ITT) principle; all individuals with evaluable data for the outcome under investigation will be analyzed in the group they were randomized to, regardless of treatment received. Additionally, ‘per protocol’ (PP) analyses will be conducted where there have been large deviations from the planned intervention; all individuals with evaluable data for the outcome under investigation will be analyzed according to the treatment received. Any such analyses will be clearly labeled as such and cautiously interpreted as perhaps indicating the maximum theoretical potential of these programs. The PP analyses will consist of three comparison groups according to the timing of the treatment received. The three groups are ‘intervention early’, ‘intervention late’, and ‘no intervention’. The ‘intervention early’ group will consist of individuals whose teachers reported they received their *Ask Health Diary* at the time they were scheduled to, or within 3 months of the time they were scheduled to, and parents/carers confirmed this had been received. The ‘intervention late’ group will consist of individuals who teachers reported they received their *Ask Health Diary* at least three months later than they were scheduled to and those who, when their parents/carers were contacted in July 2008, reported they had not received a diary. The ‘usual care’ group will consist of individuals randomized not to receive an intervention. The separate effects of the CHAP health check, the *Ask Health Diary* and the *Ask Project Curriculum Strategy Booklet* will be explored by comparing outcomes for individuals according to the number, and timing, of components of the health intervention package they received.

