#### Exit surveys

Seventy-four (57.4%) of the 129 teacher exit surveys mailed were returned for analysis (See Figure
2a). Only 26 teachers reported that they began teaching the project in Term 1; 34 did not do so until Term 2; and others began even later in the year. Teachers also differed in the number of hours per week and the number of weeks taught. 47 teachers taught for one semester only, 23 taught over 2 semesters and 4 taught over 3 semesters. On average teachers taught for 11 weeks (SD = 7) and for 57 minutes per week (SD = 28).

Most diaries were not sent home from schools until June/July 2007, but others were not sent until third or in at least two cases fourth term. CHAP booklets were sent to carers of the intervention participants after all schools reported that the diaries had been sent home so that they might take their child to their doctor for the health check in November 2007. These delays required a revision of the original project timeline (Figure
1). Figure
3 shows the actual timeline.

Between Baseline and the Exit many participants were lost to follow up and 41 had no consenting GP so could not continue in the study. Of the 347 adolescents from the intervention group who completed the baseline survey, only 176 returned their CHAP booklets. Of the 486 carer exit surveys sent out in July 2009, 388 (79.8%) were returned (See Figure
4).

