##### Health outcome data

GP records were collected for 436 of the participants (See Figure
5). Depending on the time of collection and whether or not all GPs the adolescent had attended during the period had consented to participate in the study, data is available for each participant for a period up to 54 months between January 2006 and June 2010. Data was obtained for 195 of the usual care group, 161 of the intervention group who had completed both the educational and medical components of the intervention and 80 who had the educational intervention only, i.e. they did not do the CHAP.

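### The secondary 'per protocol' groups ignore the CHAP and are not randomised, so they cannot show the package's full potential, and the effects of its three components cannot be separated

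*Protocol article*

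**What the plan says.** The Trial design and Intervention sections of the protocol article define the package as three things: the diary, the curriculum booklet and the CHAP health check.

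The Quantitative part of the Analysis section makes intention-to-treat primary. Where delivery departed greatly from plan, it adds analyses by treatment received: "The PP analyses will consist of three comparison groups according to the timing of the treatment received".

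- 'Early' needs a teacher report that the diary arrived on schedule or within three months of it, plus carer confirmation of receipt.
- 'Late' takes teacher-reported delays of at least three months, and carers who said in July 2008 that they had no diary.
- The comparator is everyone randomised to usual care.

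The results are to be labelled and "cautiously interpreted as perhaps indicating the maximum theoretical potential of these programs". The only modelling features described are cluster and matching effects.

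The same section says that the separate effects of the CHAP, diary and booklet "will be explored by comparing outcomes for individuals according to the number, and timing, of components of the health intervention package they received".

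Under Results, the Health outcome data section lists GP data for 195 usual-care participants, 161 intervention participants with both education and CHAP, and "80 who had the educational intervention only, i.e. they did not do the CHAP".

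**The concern.** A treatment-received analysis should classify people by the treatment they received. This one classifies them by one component of three. Someone whose diary came on time but who never had the health check counts as 'early'. Someone who had the check but whose diary was delayed counts as 'late'. The CHAP is the component that prompts the GP examination, and the health outcomes are read from GP records, so this omission bears directly on the outcome.

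The early and late groups also form after randomisation, and only in one arm. The usual-care arm passes no matching filter, so randomisation no longer protects the comparison.

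The plan nevertheless offers the result as a possible upper limit on what the programme can do, and offers the component contrasts as separate effects. Large departures from plan did occur: 176 of 347 CHAP booklets were returned (50.7%), and 44% of carers were unaware of the diary when contacted. The condition for running these analyses therefore appears to be met.

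**Working it through.** **1. The plan's own figure.** The Sample size section gives detection of vision or hearing impairment that "has a current rate of around 10% in this population", and states that "the study would have 90% power to detect an increase in the detection of vision impairment to 19% due to the intervention". Its significance threshold is 5% (two-sided assumed; the article does not say).
- Design effect = 1 + (20 − 1) × 0.03 = 1.57.
- Effective size per arm = 500 / 1.57 = 318.5. Power for 10% against 19% = 89.9%.
- Conversely, 320 per arm × 1.57 = 502.

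The stated 90% reproduces and is not in dispute. It supplies a yardstick of 9 points. The article gives no figure for the treatment-received or component analyses.

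**2. Who has GP data.** 195 + 161 + 80 = 436, as stated. The intervention arm contributes 161 + 80 = 241.
- CHAP done: 161 / 241 = 66.8%.
- CHAP not done: 80 / 241 = 33.2%.

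These are shares of all intervention participants with GP data. The article does not give the CHAP share within 'early' or 'late'.

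**3. Diary status and CHAP status come apart.** The Exit surveys section of the Results says CHAP booklets went to carers in the intervention arm once all schools had reported sending diaries home, so a participant's own diary timing did not govern CHAP timing. Among the sixteen carers interviewed, all had done the CHAP but only eight reported a diary from school. This is a small convenience sample, but it shows that one does not stand in for the other.

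**4. Dilution (illustration).** Assume that the 10% to 19% effect acts only through the CHAP and that uptake is unrelated to diary timing.
- Rate in a diary-defined group = 0.10 + 0.668 × 0.09 = 0.160.
- The apparent gain is 6.0 points, not 9.

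**5. Selection with no true effect (illustration).** Assume that CHAP-takers and non-takers differ in underlying detection rate by a gap of 2 to 9 points, with an arm average of 10%.
- CHAP against education only shows the whole gap: +2 to +9 points.
- CHAP against usual care shows (1 − 0.668) × gap: 0.332 × 2 = 0.7 up to 0.332 × 9 = 3.0 points.

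The article gives no basis for choosing a value in this range. Steps 4 and 5 push in opposite directions, so the net sign is unknown.

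**6. Separate effects.** The listed groups are education plus CHAP, education only, and usual care. No group had the CHAP alone. The booklet was a teacher resource used with the diary, so those two cannot be told apart. What remains is mainly CHAP against education only, and the Discussion reports that families often did not take the adolescent for the review.

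**7. Precision.** Power for 10% against 19% with the group sizes in step 2, first without clustering, then with design effect 1 + (436/76 − 1) × 0.03 = 1.14 (76 = 41 + 35 schools):
- CHAP against education only: 43%, then 38%.
- CHAP against usual care: 68%, then 62%.
- Education only against usual care: 53%, then 48%.

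**The case against.** The plan is candid. Intention-to-treat is primary, the additional analyses are labelled and hedged, and component effects are only to be explored. An article may also leave covariate adjustment to a fuller analysis plan. All this stands and limits the seriousness of the point. It does not mend a stated definition that omits a component, nor does it make inseparable effects separable.

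Several stronger readings are tempting, but the article does not support them.

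- *Both analyses use diary timing alone.* This is true only of the early/late grouping, which also uses carer reports of receipt. The component analysis counts components, so the CHAP enters there.
- *The early and late groups are self-selected.* CHAP uptake was a family decision, but diary timing was set mainly by schools and teachers. 'Non-randomised' is the accurate word.
- *The contrasts will look strongly positive even if the package does nothing.* Selection may inflate them, but missing CHAPs dilute a real effect, and neither size is documented.
- *Many participants cannot be classified.* The article reports: "Seventy-four (57.4%) of the 129 teacher exit surveys mailed were returned for analysis". The 55 / 129 = 42.6% not returned counts teachers, not students. The article does not say that diary timing came from that survey, and schools also reported on diaries separately.
- *CHAP against no CHAP means families who saw the GP against families who did not.* All 80 education-only participants have GP data. The article says only that they did not do the CHAP.
- *A complier-average estimate should replace the analysis.* With CHAP as receipt, it assumes that teaching and diary do nothing without the CHAP, which the package's design makes doubtful. More usual-care than intervention schools withdrew after randomisation, and GP data cover 241 / 425 = 56.7% of the intervention arm against 195 / 303 = 64.4% of usual care. Nor is CHAP status shown to be known for every participant.

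**Conclusion.** The point holds for the secondary analyses and leaves the primary analysis and the sample size untouched. The treatment-received definition omits the CHAP, which 33.2% of intervention participants with GP data did not do. It compares groups formed after randomisation with an unfiltered usual-care arm. The result estimates neither a full-package effect nor a ceiling on it. The separate effects of the three components cannot be identified from the groups listed.

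The 33.2% is documented. The 6.0-point diluted gain and the 0.7 to 9 point selection range are illustrations resting on the assumptions in the working. They show that the bias could be large relative to the 9-point design difference, not which way it goes. The change is worth making, though the plan's own caution keeps it from being critical.

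**What to change.** - Keep intention-to-treat primary.
- Define treatment received by diary receipt and by CHAP completion where that is documented, and say how undocumented CHAP status is handled.
- Report the early/late and component contrasts as non-randomised and descriptive. Adjust them for age, school type and GP activity before baseline; records were requested from January 2006 and the trial opened in February 2007. Adjustment reduces the confounding but does not remove it.
- Drop both the maximum-potential interpretation and the promise of separate effects. Describe the main component contrast as CHAP against education only among families who decided whether to attend the review.
- Optionally add a complier-average estimate with randomised arm as instrument, as a sensitivity analysis only. State its doubtful exclusion assumption (no effect of teaching or diary without the defined receipt), the differential school withdrawal and the wider intervals.

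The cost is revised wording, slightly more analysis and a weaker secondary claim. No new data collection is needed.

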## Results

### Recruitment

Data were provided by Education Queensland as to the number of students in the 160 SESs and SEUs that met the inclusion criteria. Of the 160 schools, 59 were excluded as 49 had enrolments of less than 10, one had participated in the pilot project, six had student populations that were transient in nature and three schools were considered too remote. The recruitment officer contacted all eligible schools and offered to do a presentation for teachers. Of the 101 schools approached, 16 schools declined. Of these 10 considered it too difficult to incorporate the project into what was often an already over-crowed curriculum, two special education units thought it too simple for their students and four gave no reason (See Figure
2a).

**Figure 2 F2:**
[figure not shown]
a Participant Flow – Educators, b Participant Flow – Adolescents and Carers.

### Intervention

The program was scheduled to be taught in schools in the first term of 2007, but changes in the way teachers were allocated to schools at the beginning of that year meant that in first term there were major staff changes and, as a result, after randomisation but before we had sent out baseline surveys, we saw nine schools withdraw from the study. All schools reported difficulty in obtaining student consent, but more usual care schools than intervention schools withdrew from the study (See Figures
2a and
2b). New teachers in special education units randomised to the intervention group considered it appropriate to teach the program to incoming Grade 8 students which resulted in the inclusion of 12 year old adolescents in the study. Because of the organisational structure of special schools, some even younger students were also included which led to the revision of our age eligibility criteria to 10–18.

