### Participants

Participants were drawn from Special Education Schools (SESs) and Special Education Units (SEUs) in Southern Queensland. Children were eligible to participate in the study if they had been assessed by Education Queensland to have an intellectual disability, were aged 10 to 18 years as at 1 January, 2006, and were registered at Education Queensland SESs or SEUs located in Southern Queensland. In Queensland, children who have an intellectual disability may receive their education in a segregated special school for children who have a disability (SES) or in a special education unit or class that is on the campus of a mainstream primary or secondary school (SEU). Students who attend a special school have significant intellectual disabilities and/or multiple disabilities, and usually require specialist teaching and therapy services that support an individualised education program. A small number of these special schools are designated as “High-Support Needs Special Education Schools” and have the staff and specialised facilities required for children with profound disabilities. Students who attend a special education unit in a primary or secondary school may have a range of disabilities, and usually access the mainstream curriculum and receive specialist teaching and therapy services. The choice of placement options for students with disabilities can be influenced by a range of factors, such as parent choice and education options available in the local area.

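### The age criterion was widened after randomisation, partly through a decision in intervention units, so age may be imbalanced between arms and the models as described name no age term

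*Protocol article*

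**What the plan says.** The Sample size section builds its frame on the older age band: "We estimated there would be 2,403 adolescents aged 13 to 18 years and registered at SES or SEU". The Participants section gives a wider one, saying that eligible children "were aged 10 to 18 years as at 1 January, 2006", with no note that this is a revision.

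The Results section headed Intervention gives the history. Staffing changed at the start of the 2007 school year, and "after randomisation but before we had sent out baseline surveys, we saw nine schools withdraw from the study". It continues: "New teachers in special education units randomised to the intervention group considered it appropriate to teach the program to incoming Grade 8 students". Pupils aged 12 entered the trial by this route. A second source follows, with no arm named: "Because of the organisational structure of special schools, some even younger students were also included". The age rule was then changed to 10–18.

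The Randomisation section stratifies by school type and location, then pairs schools by expected number of participants. Age plays no part. The Quantitative analysis section describes mixed-effects models "with allowance made for cluster and matching effects" and names no other terms. Its primary analysis is by intention to treat, using everyone with evaluable data. The Baseline surveys section shows that carers were asked for the adolescent's age.

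**The concern.** In a cluster trial, randomising schools protects the comparison of individuals only if the pupils who enter do not depend on the arm. Here the units already knew that they were to teach the program, and teachers in some of them chose which grade to teach. Usual care schools had no program to teach, so that particular choice did not arise there. Pupils below the planned age range could therefore have entered one arm more often than the other.

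The outcomes taken from GP records include immunisations, health screening, and smoking and alcohol consumption. It is reasonable to expect some of these to vary with age, although the article gives no age-specific rates. If they do, an age difference created after allocation would be read as part of the intervention effect.

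**Working it through.** **1. The plan's own figure.** Inputs from the Sample size section: 500 pupils per arm, mean cluster size 20, ICC 0.03, rates 10% and 19%, 5% significance (two-sided assumed).

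- Design effect = 1 + (20 − 1) × 0.03 = 1.57, as stated.
- Effective number per arm = 500 / 1.57 = 318.5.
- Power for 10% against 19% = 0.899, against the stated 90%.

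The figure reproduces. The yardstick for any bias is the planned difference, 19 − 10 = 9 points.

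**2. What the text ties to an arm.**

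| Step in Results, Intervention | Arm named? |
|---|---|
| Grade 8 pupils taught, 12-year-olds enter | Yes, intervention units |
| Even younger special-school pupils enter | No |
| Criterion revised to 10–18 | Follows from the above |

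Only the first step is linked to allocation.

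**3. Would the named model terms deal with it?** Each pair holds one intervention and one usual care school. A pair effect removes what the two schools share: type, location and approximate expected size. A school effect allows for correlation within a school. An age difference that follows the allocation lies within the pairs, in the same direction as the treatment contrast, so neither term removes it.

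**4. How large could it be?** No ages by arm are given, so this is an illustration. Let f be the excess share under 13 in the intervention arm and d the difference in outcome rate between the age bands. The unadjusted shift is f × d; its sign depends on the outcome.

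| f (assumed) | d = 2 points | d = 5 points | d = 10 points |
|---|---|---|---|
| 5% | 0.1 | 0.25 | 0.5 |
| 10% | 0.2 | 0.5 | 1.0 |
| 20% | 0.4 | 1.0 | 2.0 |
| 30% | 0.6 | 1.5 | 3.0 |

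The range is 0.1 to 3.0 points, or 0.1/9 = 1% to 3.0/9 = 33% of the planned difference. If these pupils were on average 3 years younger (assumed), the arms' mean ages would differ by 3f, or 0.15 to 0.9 years.

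**5. Enrolment per school.** From the Baseline surveys results: 425/41 = 10.4 in the intervention arm and 303/35 = 8.7 in usual care. The excess is (10.37 − 8.66) × 41 = 70 pupils. Given the intervention arm's 41/76 share of schools, 728 × 41/76 = 392.7 pupils would be expected there. The observed 425 gives z of about 2.4, or about 2.1 after a design effect of 1 + (728/76 − 1) × 0.03 = 1.26. This fits recruitment that differed by arm, but it carries no information about age.

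**The case against.** Four stronger readings are tempting, and the article supports none of them.

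- **That the arms do differ in age.** No age distribution, and no count under 13, is given for either arm. Usual care schools may also have enrolled pupils under 13; the text does not say.
- **That intervention schools alone caused the widening.** The even younger pupils are put down to how special schools are organised, and no arm is named.
- **That the planned analysis excludes age.** The article summarises the models briefly and does not rule out covariates. A fuller analysis plan may list them.
- **That the excess of about 70 pupils consists of under-13s.** More usual care than intervention schools withdrew after randomisation, which broke pairs formed on expected numbers, and all schools had difficulty with consent. Either could produce the excess.

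It is also fair to say that the article discloses the revision and its reasons openly. Nor would it be right to make 13 to 18 the primary analysis set. That would replace the stated intention-to-treat analysis with a later exclusion, under a rule that the article gives only as a planning population and without a reference date.

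What stands is the article's own account that a decision in intervention units, after allocation, brought in pupils below the planned ages. That risk does not depend on any of the four readings.

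**Conclusion.** The point holds as a documented risk, not as a demonstrated bias. After randomisation the age criterion went from the planned 13–18 to 10–18, partly through a choice made only in intervention units. Age may therefore be imbalanced by selection, and the terms named in the models would not correct for it. The actual size is unknown. The range of 0.1 to 3.0 points against 9 rests wholly on assumed values for the excess share of under-13s and for the gap in outcome rates between age bands. At the low end it is negligible; at the high end it is a third of the planned difference. The analysis is described in the future tense, so a protective change can still be made at little cost.

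**What to change.** - Add baseline age as a fixed effect in the outcome models. Take it from the carer survey, or from school records where the survey is missing.
- Report the age distribution and the number under 13 by arm.
- Keep the stated intention-to-treat set as primary. Add a sensitivity analysis restricted to ages 13 to 18 in both arms.
- Fix one reference date for that restriction. The choice matters: the criterion uses 1 January 2006 while teaching was scheduled for the first term of 2007, so a pupil aged 13 in February 2007 was 11 or 12 on the criterion date.
- In the Participants section, state that 10 to 18 is a post-randomisation change.

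The cost is a little more analysis and some loss where age is not recorded. The Exit surveys results mention 347 intervention adolescents with a completed baseline survey, against 425 in that arm at baseline. If age came from that survey alone, up to 425 − 347 = 78 (18%) could lack it, hence the school-record fallback. That schools can supply age is an assumption. If very few usual care pupils are under 13, the age term has to extrapolate, and the restricted analysis is then the more informative check.
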